**Enrollment**							
	Eligibility screen	✓					
	Informed consent	✓					
	App installation	✓					
	Allocation				✓		
**Interventions**							
	App use			✓		✓	
	Sensor use			✓		✓	
	Microinterventions			✓		✓	
**Assessments**							
	VEDAS^g^		✓		✓		✓
	HRV^h^			✓		✓	
	Profile			✓			
	EMA^i^ (morning, interval, and evening)			✓		✓	
	CSAT^j^, SUS^k^, PSM^l^, and feedback				✓		✓

^a^T0: baseline.

^b^T1: before P1.

^c^P1: first 3-week phase.

^d^T2: between P1 and P2.

^e^P2: second 3-week phase.

^f^T3: after P2.

^g^VEDAS: Valencia Eustress-Distress Appraisal Scale.

^h^HRV: heart rate variability.

^i^EMA: ecological momentary assessment.

^j^CSAT: customer satisfaction score. The CSAT was expanded with 3 additional items.

^k^SUS: System Usability Scale.

^l^PSM: price sensitivity meter.

#### Primary Outcomes

First, primary outcomes were the emotional state over the course of the study and self-reported experience of chronic stress. On the one hand, levels of emotional states and stress were recorded daily using the ecological momentary assessment (EMA) technique. The data obtained from the daily subjective interval, morning, and evening interval questionnaires were used as a diagnostic tool. These questionnaires were developed internally, with established psychometric instruments used in certain cases. A team of experts was responsible for selecting the items for the internally developed instruments, some of which were commonly used items for the topics in question. Emotional state was assessed on the basis of the 2 dimensions: arousal and valence. In the interval questionnaire, in addition to the current state experienced at the time of entry, the state at a possible last stress event was also recorded in a similar manner.

The experience of chronic stress was evaluated using the evening questionnaire, which included items from the Chronic Stress Screening Scale [53] and the Leipzig Screening Questionnaire on Chronic Stress [54]. The Chronic Stress Screening Scale items assessed feelings of lack of satisfaction and high demands, while the Leipzig Screening Questionnaire on Chronic Stress items focused on experiences of loss of control, inability to recover, and negative emotions. The EMA questionnaires were each scored on a 7-point Likert scale. Conversely, chronic stress was evaluated using the Valencia Eustress-Distress Appraisal Scale [55] at the following time points after P1 and P2 in the web-based questionnaire. The questionnaire was used to distinguish between work-related distress and eustress, as well as to evaluate the subscales of relationship, personal accountability, work-life balance, and workload. A 6-point Likert scale was used in line with the original instrument.

Second, the physiological stress parameters, as measured by the Polar VS sensor, were recorded as primary outcomes. Similarly, the continuous data from the app use were used as an outcome. The stress parameters were HRV variables: SD of r-r-intervals, which is a direct measure of HRV; RMSSD, which is a measure of the parasympathetic recovery capacity; and LF/HF, which is the ratio of the balance between the sympathetic and parasympathetic nervous systems in favor of the latter.

Third, the level of satisfaction was assessed using the web-based questionnaire administered after P1 and P2. In this instance, the customer satisfaction score [56] was expanded with 3 supplementary items that were specifically designed to assess satisfaction and effort with the Relax approach. The items included ratings for overall satisfaction, workday adaptability, exertion due to EMA, and exertion due to sensor handling. The participants were required to indicate their level of agreement with the statements on a 5-point Likert scale.

Fourth, the System Usability Scale [57] was used to assess usability in the web-based questionnaire at P1 and P2. The items that were specifically reformulated for the Relax approach were collected using a 5-point Likert scale.

#### Secondary Outcomes

The interval questionnaire also included items on the momentary activities at the time of entry and the last stress event. The daily morning questionnaires for participants in P1 and P2 included additional items pertaining to expected stress levels for the day, as well as perceived restfulness of sleep from the previous night and the frequency and duration of sleep disruptions. The evening questionnaires inquired about the summarized emotional state along with well-being and the summarized activities of the previous day.

In addition to the quantitative survey, which was used as the primary outcome measure, satisfaction was also assessed using qualitative items. A total of 4 questions with an open item format were included in the survey to elicit feedback on the use of the app and the wearable device, as well as any suggestions or comments the participants might have. Finally, participants’ price acceptance was measured in the web-based questionnaire using the price sensitivity meter [58].

Within the displayed daily questionnaires, plain text fields allowed participants to report stressful events and special circumstances from the day. These responses were catalogued by the backend service and stored in the web-based database. However, they were not automatically analyzed by the system at this early stage of app development. Future research may explore automated analysis of stress-related text responses.

### Data Management

To prevent loss of the sensor data and ensure continuous 24/7 recording without gaps, a specialized workflow was designed for the app. All data were first stored locally on the VS system. Whenever a Bluetooth connection to the Android phone was established, a secure bulk transfer of all saved files was initiated, with a watchdog mechanism ensuring complete data reception. Once transferred to the phone, the data remained stored locally until an internet connection became available, at which point it was uploaded to the database in a similar manner as the Bluetooth transfer. If any data loss was detected, the entire file transfer process was restarted. Low battery charging problems had an inbuilt early detection system to prevent writing corrupted files on both systems.

The subjective data, pseudonymized using the self-generated code, were transferred to SPSS (version 29; IBM Corp) for data analysis. Means were calculated for all scales and then statistically analyzed. For the web-based questionnaires at T1, T2, and T3, exclusive values were created for the scales. The continuous daily data from P1 and P2 were transformed into weekly means for progression analysis. The broad time span of 1 week was intended to compensate for any missing data that were expected with complex EMA data collection integrated into daily life [60]. In addition, the general adherence to possible EMA entries and wearable data will be taken into account in the following statistical analysis. The records of individuals with at least >80% missing data will be excluded from the calculations. Data are available on reasonable request.

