### Randomization

The randomization process was conducted midway through the study, following the scheduled break. No data from P1 were used to balance the randomization in any way. The participants were randomly assigned to the groups *local* and *global*. For the group *local*, the intervention weight matrix was primarily affected by participants’ own ratings, while the ratings of all participants affected the weights for the group *global*. The group *local* was regarded as the group with greater personalization than the group *global*, given that the personalization in question was based on the individual inputs.

The participants were not informed of their group allocation, which meant that they were considered blinded. As the randomization was conducted by a separate subgroup of the study team from those involved in the study itself and the data analysis, the latter 2 parts of the study can also be described as double blinded. The evaluation of the data in pseudonymized form further enhanced this aspect of independence.

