The level of individualization of interventions in the respective experimental group was characterized by a variation in automatic individualization with regard to the interventions offered by the learning agent. Due to intentionally high α values during the adjustment of the intervention weight matrix, the *local* group had the possibility of significantly influencing their intervention delivery within 3 weeks, while the group *global* would only perceive minor changes. α-local describes the extent to which a rating changed the weight of an intervention for a single user. For the group *global*, it was set to 1.0 (no change to the user’s own weight), and for the group *local*, it was set to 2.1. The weights were adapted using the following formula: new_weight=old_weight * (alpha_local^old_weight). α-global describes the extent to which a rating changed the weight of an intervention for all users. It was set to 21 for both groups. The weights were adapted using the following formula: new_weight=old_weight *(alpha_global^(old_weight/number_of_users)).

Data entry was continuously monitored by the study team throughout the weeks. Participants were encouraged to continue their engagement through regular emails from the study team. It was expected that a general increase in adherence would be achieved as these messages were sent to all participants equally. If technical problems occurred, they were addressed individually via the app and generally via email. It is assumed that such individual correspondences would not add to the overall bias of the user experience since the individual disruption was already a bias, which is not uncommon in pilot studies. In P1, an update of the app was offered in the second week, which solved the technical problems that had arisen up to that point. Participants were given support to reinstall the app, and a self-help guide for the most common technical problems was offered. During the break between P1 and P2, additional technical difficulties were overcome by the study team, and when feasible and relevant, the participants’ input thus far was considered. Following this adaptation of the system in accordance with feedback, a graphical overview of the sensor data was made available in P2. This enabled the participants to maintain awareness of the data and its evolution over time.

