### Statistical Analysis

To statistically analyze the central evaluation questions of the prototype developed in the Relax project in terms of its efficacy in reducing stress in the workplace, different models will be constructed. First, the difference between the groups and thus the degree of individualization by the app will be determined. Second, the pre-post design will be used to ascertain whether the individuals exhibited a reduction in stress over time. These 2 approaches will use all stress-relevant outcomes to make assertions about the work stress of the individuals, namely the emotional states, self-reports on chronic stress as well as distress and eustress, and the physiological parameters. Linear mixed models will be used for the effectiveness analyses.

To address the usability and feasibility of the prototype, the data obtained from the satisfaction and usability scales will be used. These will also be analyzed between the groups and in the pre-post design. Exploratory analyses will test the secondary outcomes for possible effects. Additional moderation and mediation analyses will be possible here, in which the variables from the demographic and profile surveys could also be used. It is anticipated that the qualitative data from the user feedback will provide information about the specific background of the participants’ usability ratings.

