A special case is that, due to the individual personalization, the user experience may vary considerably from one individual to another, which can be challenging for an evaluation on a group basis. The fact that virtually every user could create a different experience in terms of the quantity and timing of the interventions can result in heterogeneous outcomes. Such heterogeneous results are desirable in analyses where individual personalization is a means to a general end, such as stress reduction or satisfaction with the app. In such cases, personalization must necessarily be heterogeneous due to the heterogeneity of personal stress experiences. However, such a heterogeneous user experience could lead to the app being perceived as unusable, for example, by users who experience little stress and therefore little interaction with the app.

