### Limitations

The study design reveals some limitations in the significance of the results that are still to be analyzed. First, the pilot nature of the study permits only an initial impression of the effectiveness of the developed system in terms of stress reduction in an individual context. The absence of a control group without interventional procedure precludes certainty that any effects are undoubtedly attributable to the intervention. It is possible that the potential effects on stress reduction during the study period may be influenced by factors unrelated to the intervention. Consequently, a subsequent investigative study using a controlled design is imperative to clarify the causes of any effects.

Furthermore, the unspecified ad hoc sample represents a limitation. No distinction was made between professions and sectors, which means that user experiences can vary considerably not only due to individual characteristics and stress levels but also due to the specificities of individual everyday working lives. These can partly determine the degree of interaction with the app due to varying degrees of availability of the individual for using the app during working hours. It is therefore anticipated that adherence may vary considerably among individuals who are not able to adhere to the app use instructions and are unable to wear the wearable device continuously. The small sample size will not allow for subgroup analysis, as a highly variable sample is expected in this regard. However, it is also expected that the personalization approach of the app will adapt to the highly heterogenous work lives and still create the optimal experience for each individual user.

Another limitation of this study is that data collection was conducted exclusively on Android devices. This decision was driven by technical constraints, including iOS restrictions on background data access and sensor use, as well as the greater flexibility of Android for research applications. In addition, cost considerations and the higher prevalence of Android devices compared to iOS devices within our target population influenced this choice [61].

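### The >80% missing-data exclusion is undefined and, unless counted on the first phase alone, makes the randomized comparison depend on behaviour after randomization

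*Protocol article*

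**What the plan says.** The Data Management section of the protocol article sets the rule: "The records of individuals with at least >80% missing data will be excluded from the calculations". The preceding sentence adds that "the general adherence to possible EMA entries and wearable data will be taken into account in the following statistical analysis". The same section reduces the daily data to weekly means.

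On timing, the Randomization section says: "The randomization process was conducted midway through the study, following the scheduled break". P1 data therefore precede allocation and all P2 data follow it.

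The Statistical Analysis section puts the randomized contrast first: "First, the difference between the groups and thus the degree of individualization by the app will be determined". A pre-post analysis follows. Linear mixed models are planned for effectiveness, and the satisfaction and usability scales are also to be analysed between groups and pre-post. No analysis that retains all randomized participants is described.

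**The concern.** A randomized comparison is protected by keeping everyone in the arm to which they were allocated. A rule that removes people for how much data they supplied after allocation can break that protection if the arms lead to different use of the system. The arms are built to feel different: App Intervention says the local group could significantly influence what it was offered, "while the group *global* would only perceive minor changes". Limitations expects uneven use: "It is therefore anticipated that adherence may vary considerably among individuals who are not able to adhere to the app use instructions".

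Three further things are at stake.

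- **Pre-post, satisfaction and usability results.** The pre-post estimates have no comparison arm to cancel a selection effect, and descriptive satisfaction or usability levels have none either. People who hardly used the system are the most informative about poor usability, and the rule removes them.
- **Scope of deletion.** The rule speaks of the records of individuals. Read as whole-person deletion, a completed T1, T2 or T3 web questionnaire could be lost because diary or sensor data are sparse.
- **Definition.** The phrase combining at least with a greater-than sign leaves the boundary unclear, and phase, stream and denominator are not given.

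**Working it through.** **The plan's own figure.** The only design figure is the recommended sample size of 31 (alpha .05, power 0.80, d = 0.5). A two-sided normal approximation for a within-person comparison gives ((1.960 + 0.842)/0.5)² = 31.4. The exact paired t test needs 34 two-sided or 27 one-sided, and a one-sided signed-rank test with efficiency 0.864 gives 31. The figure thus fits a within-person test, although the test is not named. Nothing below depends on it; d = 0.5 serves only as a yardstick.

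**Step 1: does the rule depend on post-randomization data?** P1 and P2 are each 3 weeks. With equal expected entries per phase and missing fractions m1 and m2, overall missingness is (m1 + m2)/2. Exceeding 0.80 requires m1 + m2 > 1.6. Even with P1 wholly missing (m1 = 1), m2 must exceed 0.6. A count over both phases, or over P2 alone, therefore always depends on P2 behaviour. Only a P1-only count would not, and the text does not say that.

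**Step 2: possible bias in the group contrast.** Assume a standardized outcome that correlates rho with a latent non-adherence score, and exclude the fraction p with the highest scores. The mean of those retained shifts in size by rho × φ(z)/(1 − p), where z is the (1 − p) normal quantile. The documents give neither p nor rho, so both are assumptions.

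| p | φ(z)/(1 − p) | shift, rho 0.3 | shift, rho 0.5 |
|---|---|---|---|
| 5% | 0.1031/0.95 = 0.109 | 0.033 | 0.054 |
| 15% | 0.2332/0.85 = 0.274 | 0.082 | 0.137 |
| 25% | 0.3178/0.75 = 0.424 | 0.127 | 0.212 |

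Bias in the contrast is the difference between the arms' shifts:

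- 15% against 5%: 0.05 SD (rho 0.3) to 0.08 SD (rho 0.5).
- 25% against 5%: 0.09 SD to 0.16 SD.
- Equal p and rho in both arms: zero.

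The sign follows the sign of rho, which is unknown.

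**Step 3: check at the actual size.** Simulation used 23 against 23 (46 in total; an even split is assumed), no true effect, 20,000 runs and a two-sample t test. Excluding 1 to 5 people from one arm only, with rho 0.3 to 0.7, gave a bias of 0.03 to 0.25 SD and a two-sided type I error of about 5% to 14%. For example, 3 people and rho 0.5 gave 0.12 SD and 7.1%. Excluding 2 or 4 from each arm by the same mechanism (rho 0.5) gave a bias of about zero and an error of 5.2% to 5.5%.

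**Step 4: single-group results.** Equal exclusion does not cancel within one group. The shift columns above then apply to the retained sample itself: 0.03 to 0.05 SD at 5% exclusion and 0.08 to 0.14 SD at 15%, in SDs of whatever is analysed, such as a change score or a usability score.

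**Step 5: power.** Two-sample t test at d = 0.5, two-sided: 38% at 23 against 23, 36% at 23 against 20, and 34% at 20 against 20.

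**Step 6: weekly means.** Four required entries a day (morning, evening, two interval) make 28 a week and 84 a phase. If the denominator were these entries, 20% is 16.8, so a person with 17 would stay in, at about 5.7 entries a week. Unweighted weekly means would count such a week the same as one with 28.

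**The case against.** Several points on the other side stand.

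- **Differential missingness is not shown.** A reader might infer that missing data depend on arm. The documents do not say so. Participants were not told their allocation, encouragement emails went to all equally, the described arm difference is confined to intervention weighting, and technical failure is another named cause of lost data. The exclusion rates in step 2 are hypothetical. The threshold is lenient and compensation depended on sufficient participation, so few people may be affected.
- **The link between low stress and low use is weaker than it looks.** Anticipated Findings says "such a heterogeneous user experience could lead to the app being perceived as unusable, for example, by users who experience little stress", and refers to "users who experience little stress and therefore little interaction with the app". This concerns interaction with the app and its interventions, not missing diary or sensor data, which were required daily of everyone. If it did apply, the excluded would be the less stressed. It cannot establish a direction of bias.
- **The adherence sentence does not establish adjustment for P2 adherence.** It could mean reporting or a sensitivity analysis. It would be a defect only if P2 adherence became a covariate, weight or subset criterion in the group contrast.
- **The rule has a plausible purpose.** It is tempting to say that it gains nothing because mixed models accept incomplete records. With unweighted weekly means, the model would not recognize a sparse week as less precise, so screening out near-empty records does address data quality.
- **Whole-person deletion is one reading.** The rule follows directly on a sentence about diary and wearable adherence, so a per-stream reading is open.

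What does not stand is a defence that this is detail left to a fuller plan. The exclusion is a stated rule, with no exception for the randomized comparison.

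**Conclusion.** The point holds as a risk built into a stated rule, not as a demonstrated bias. Unless missingness is counted on P1 alone, exclusion depends on post-randomization behaviour. For the local-against-global contrast the bias is about 0.05 to 0.16 SD in size, direction unknown, under the assumed 15% to 25% against 5% exclusion and absolute correlation of 0.3 to 0.5. It is about zero if exclusion is equal by arm. Against d = 0.5 that is modest but not negligible. The pre-post, satisfaction and usability results can be selected towards persistent users even when exclusion is balanced. The power cost is small and is not the reason to change the rule. The change should be made, because the planned model does not need the exclusion in order to be fitted.

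**What to change.** - **Main analysis.** Include all randomized participants as allocated, with all available values of each outcome, in the linear mixed model. Someone with P1 data but little or no P2 data then still contributes.
- **Sparse weeks.** Model individual entries, or weight weekly means by their number of entries, so that a sparse week does not count as a full one.
- **The 80% rule.** Keep it only as a sensitivity analysis, defined per outcome stream, with phase, denominator and boundary stated. Sparse diary or sensor data should not remove a completed web questionnaire.
- **Reporting.** Give exclusions and P2 adherence by arm.
- **Adherence as covariate.** If it enters the group comparison, use P1 adherence only, since that precedes randomization.

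The Results section says the analyses are still to be carried out, so the cost is plan wording plus the weighting or entry-level step. The downside is somewhat noisier data from sparse users. Validity still rests on missing-at-random, which fails if non-response tracks unrecorded stress; comparing results with and without the exclusion shows how far the conclusions depend on the rule, but does not test that assumption.
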